### Statistical Plan

The main analysis will consist of comparing the reduction in symptoms after 6 months for the three groups: e-cigarettes with nicotine vs control; e-cigarettes without nicotine vs control; and e-cigarettes with nicotine versus e-cigarettes without nicotine. Analyses will be based on two-sided *Z* tests.

A secondary analysis will assess the reduction of the consumption of tobacco-containing cigarettes after 6 months among the groups. Analysis will be based on paired Student’s t-test or the Wilcoxon signed rank tests.

No interim monitoring is planned since, given the sample size, any interim analysis would have too few events to be interpreted. Efforts will be made to maximize retention by maximizing trust at the baseline assessment and collecting multiple means to contact and commit participants, including email and phone contact details, and by assertive follow-up. Starting with our previous experience with a similar population coming from the COSMOS I program, we expect that our participants will be compliant with and committed to the aims of the study. Giving the expected intrinsic motivation of participants and thanks to the above strategies, the study aims to have at least 80% retention at 6 months and 70% at 12 months. Considering these figures, we expect to maintain a statistical power to detect a reduction of 5 cigarettes/day in our smokers (the cigarettes per day mean is about 20 in the COSMOS population). Thus, using a two-sided two-sample *t*-test with a significance level (alpha) of .05, a sample size of 49 participants per arm will achieve 80% power to detect a mean reduction of 5 cigarettes/day between any of the 2 experimental arms and the control arm, assuming a mean consumption of 20 cigarettes/day in the control arm and a common standard deviation of 8.7.

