From a physiological point of view, e-cigarettes appear to eliminate the craving for tobacco in the same way as nicotine replacement therapy (NRT). In an overview of the Cochrane Library [4] that considered studies globally—including more than 50,000 smokers—NRT was described as being particularly efficacious for the short term (3 months) but less so in the long term (12 months). However, the use of NRT increases the success rate of quitting attempts independent of the setting if compared to attempts made by smokers on their own or supported only by counseling. Furthermore, NRT is particularly useful for smokers who are prepared to quit, but who have high nicotine dependence. Eventually, NRT will be particularly effective when smokers’ baseline conditions are predictors of successful quitting. Comparing the conclusion of the Cochrane review with the results of studies on e-cigarettes effects, it is clear that in some cases the sample used was quite different from the one used in most trials on NRT. We argue that it is necessary to study e-cigarettes efficacy while also considering population baseline characteristics as well as psycho-cognitive parameters. Indeed, we can expect smokers who are not prepared to quit or in psychosocial conditions associated with a low success rate (ie, mood disturbance, living in a context with high prevalence of tobacco cigarettes smokers, low-income status) to report a worse outcome in studies using e-cigarettes as tobacco cessation treatment [2,4].

Previous research has stressed that monitoring lifestyle parameters (in particular, physical activity and sleep quality) and acting on them could help maintain abstinence. In particular, physical exercise may aid smokers in the first 3 months, while longer effects are less clear [5]. It has been observed that regular physical activity among smokers reduces nicotine withdrawal symptoms and craving. Last, smoking during the night is an indicator of nicotine dependence and predicts failure in smoking cessation [6]. Sleep disturbances have several negative psychological effects, including reduced quality of life and psychological distress (ie, anxiety and depression). Low sleep quality due to abstinence is a predictor of a poor smoking treatment outcome [7].

Low-cost, noninvasive devices are now available to monitor lifestyle parameters. These electronic bracelets are reliable and easy to use. Counseling approaches based on similar tools have been shown to improve outcomes [8].

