#### Instruments

Self-reported measures are used for cough and other respiratory symptoms assessment. We opted for Likert scales to measure cough, breath shortness, mouth irritation, and phlegm frequency as well as the Leicester Cough Questionnaire.Fagerstrom Test for Nicotine Dependence: a 6-item self-reporting questionnaire assessing nicotine dependence. It requires a few minutes to complete [12]. This test is administered to all COSMOS II participants.Motivational questionnaire [13]: a 4-item self-reporting questionnaire assessing motivation to quit smoking. The total classifies the patient into 1 of 4 motivational categories (from “not ready to quit” to “highly motivated”). This test is administered to all COSMOS II participants.Hospital Anxiety and Depression Scale (HAD): The HAD is a self-administered questionnaire composed of two 7-item scales, 1 for anxiety and 1 for depression, which should be used as 2 separate measures of emotional distress. The scale has been validated for Italian culture by Costantini and showed high internal consistency with Crohnbach alpha, ranging from .83 to .85 [14]. The HAD evaluates symptoms of anxiety and depression, avoiding misattribution due to the physical aspects of the illness. The values range from 0 to 21 for each scale. Cutoff scores are preliminarily defined as normal (0-5), mild (6-8), moderate (9-11), and severe (greater than 11) for both anxiety and depression patients [15].BIS/BAS Scale [16]: a 20-item self-reporting questionnaire evaluating the behavioral inhibition system (BIS) and BAS. Each of the items is rated on a 5-point scale, ranging from 1 (does not describe me at all) to 5 (describes me very well).Barratt Scale [17]: an 11-item self-reporting questionnaire designed to measure impulsiveness. All items are measured on a 4-point scale (Rarely/Never; Occasionally; Often; Almost Always/Always), where a 4 generally indicates the most impulsive response, although some items are scored in reverse order to avoid a response bias [18].The Leicester Cough Questionnaire: a valid, self-reported cough-specific health status measure. It is a 19-item questionnaire that has been validated in acute and chronic cough [19]. The overall score ranges from 3 to 21 with a higher score indicating a better quality of life.Electronic bracelet (the Flex FitBit): a device that allows lifestyle monitoring of physical activity and sleep characteristics, including: sleeping and napping (hours slept, light vs deep sleep, and waking periods); activity (distance, calories burned, activity time, and activity intensity); nutrition (food and beverage intake); mood (assessment of the affect state); and an insight engine that identifies hidden connections and patterns in day-to-day activities.The exhaled CO is measured by the The Micro+ Smokerlyzer, which has less than 5% H_2_ cross-sensitivity.Ad hoc questionnaire: measures demographic data, self-perceived quality of life (analogue scale), physical activity, and smoking-related issues (characteristics of the smoking experience).

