
### Recruitment and Follow-Up

All inclusion and exclusion criteria are checked during the registration procedure and initial assessment for inclusion in COSMOS II. Eligible participants are asked to provide informed consent. The informed consent form is signed and dated by both the participant and the physician. Enrolled participants receive a chronological number and are assigned to a treatment group (e-cigarettes with nicotine, e-cigarettes without nicotine, or control).

A randomization list using a permuted block design (40 blocks of 6 subjects randomly assigned to 1 of the 3 treatment groups) have been previously prepared by an independent personnel unit and labeled with the progressive number applied to the packaging containing e-cigarettes and liquid cartridges with or without nicotine (Group 1 and Group 2).

Neither the participant nor the researcher in charge knows whether the liquid in the e-cigarettes kit contains nicotine. Only the statistician who prepared the randomization list and the person labeling the e-cigarettes packaging know the actual treatment.

Each participant is then assigned to one of the three groups and receives the related treatment, as illustrated above.

Follow-up: 6 months (at the IEO)

Behavioral psycho-cognitive questionnairesClinical parameters assessment (respiratory symptoms)Smoking status assessment (questionnaire and CO level). The nonsmoking status is established by self-report items and the CO level (ppm<5).Debriefing, during which we also ask participants of Group 1 and Group 2 to guess if they used a nicotine-free or a nicotine-based e-cigarette.

End-point: 12 months (at the IEO, during the annual assessment of COSMOS II)

Clinical parameter assessment (respiratory symptoms)Final behavioral and psycho-cognitive assessmentSmoking status assessment (questionnaire and CO level)Debriefing and collection of comments

Timeline (Figure 2):

Distribution of e-cigarettes: 3 months (ends at Week 12)Data tracking (e-bracelet) and active monitoring: 6 months (ends at Week 24)End point: 12 months

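### The cigarette-consumption analysis is meant to compare the arms but names paired, within-arm tests; a between-arm ANCOVA on baseline values already collected would repair this and may add some precision

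*Protocol article*

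**What the plan says.** All references are to the protocol article.

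- **Statistical Plan, primary outcome.** Symptom reduction at 6 months is compared pairwise among the three arms: "Analyses will be based on two-sided *Z* tests".
- **Statistical Plan, cigarette consumption.** The aim is a comparison of arms: "A secondary analysis will assess the reduction of the consumption of tobacco-containing cigarettes after 6 months among the groups". The method follows at once: "Analysis will be based on paired Student’s t-test or the Wilcoxon signed rank tests".
- **Statistical Plan, power for cigarette consumption.** The calculation is made "using a two-sided two-sample *t*-test with a significance level (alpha) of .05", with 49 per arm, a difference of 5 cigarettes/day between an e-cigarette arm and control, a control mean of 20 and a common SD of 8.7.
- **Recruitment and Follow-Up.** Allocation uses a "permuted block design" with blocks of 6. No stratification factor is named.
- **Instruments.** Of the Fagerstrom test the article says: "This test is administered to all COSMOS II participants". Smoking-related questions are in the ad hoc questionnaire, and Treatments Common to All Groups lists a baseline behavioral evaluation.
- **Secondary Outcome Measures.** Daily cigarette number is defined as a change, so a baseline value exists.
- **Introduction.** The authors argue that "it is necessary to study e-cigarettes efficacy while also considering population baseline characteristics as well as psycho-cognitive parameters".

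None of the tests named contains a covariate.

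**The concern.** There are two linked problems, and the first is the more serious.

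**The named test does not answer the stated question.** A paired t-test or a signed rank test asks whether smoking in one arm changed from baseline. All three arms contain motivated smokers who receive counseling, so each arm could show a significant fall with no difference between arms. One arm could also reach significance and another miss it without the two differing significantly. Followed literally, the plan gives three within-arm results and no estimate of the treatment effect on consumption, although the sample was checked against a two-sample test of exactly that effect.

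**Baseline information goes unused as a covariate.** Baseline cigarettes/day and the Fagerstrom score are on hand before randomization. Since the test must be rewritten in any case, a between-arm model that includes them costs almost nothing more and can narrow the confidence interval.

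**Working it through.** **1. Question, test and power basis side by side**

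| Element of the Statistical Plan | What it addresses |
|---|---|
| Aim for cigarette consumption | Difference among arms at 6 months |
| Named tests (paired t, signed rank) | Change from baseline within one arm |
| Power statement (two-sample t) | Difference between two arms |

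The aim and the power statement agree. The named tests fit neither.

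**2. Reproducing the plan's figure**

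Inputs from the Statistical Plan: difference 5, SD 8.7, two-sided alpha 0.05, power 80%. The standardized difference is 5/8.7 = 0.575. The exact two-sample t-test needs 48.5 per arm, rounded up to 49, and 49 per arm gives 80.4% power. The stated 49 is correct for an unadjusted two-sample comparison. It also equals 70% of 70, the 12-month retention target; the 6-month target of 80% leaves 56.

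**3. What covariate adjustment could add**

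Let r be the joint (multiple) correlation of the baseline covariates with the outcome. The residual SD is 8.7 × √(1 − r²). The article gives no r, so it is varied.

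| Assumed r | Variance removed (r²) | Residual SD | Power, 49 per arm | Power, 56 per arm |
|---|---|---|---|---|
| 0 | 0% | 8.70 | 80.4% | 85.4% |
| 0.1 | 1% | 8.66 | 80.8% | 85.8% |
| 0.2 | 4% | 8.52 | 82.0% | 86.8% |
| 0.3 | 9% | 8.30 | 83.9% | 88.5% |
| 0.5 | 25% | 7.53 | 90.2% | 93.6% |

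At 49 per arm the gain is 0.4 to 9.8 points, and at most 3.5 points for r up to 0.3. Here r belongs to baseline cigarettes/day and the Fagerstrom score together. The table does not show what the Fagerstrom score adds alone.

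**4. Comparison with a change score**

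The r = 0 row makes no use of baseline, whereas the article defines the outcome as a change. Suppose baseline and Month 6 consumption have equal variance σ² and correlation ρ. The change score then has variance 2σ²(1 − ρ), and ANCOVA on baseline alone has σ²(1 − ρ²). The ratio of ANCOVA to change score is (1 + ρ)/2: 0.65 at ρ = 0.3, 0.75 at 0.5 and 0.85 at 0.7. ANCOVA is never worse, but where ρ is above 0.5 the change score has already taken part of the gain.

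**5. Why the primary outcome is treated differently**

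Read the Sample Size section's 5% and 20% as proportions improving; this is an assumption, as the wording allows other readings. With 80% retention of 70, each arm has 56. Expected events are 56 × 0.05 = 2.8 in control and 56 × 0.20 = 11.2 in an e-cigarette arm, about 14 in a pairwise comparison. The chance of no control event is 0.95⁵⁶ = 5.7%, and in that case a logistic treatment coefficient cannot be estimated by ordinary maximum likelihood. A model with treatment and two covariates is fragile on so few events.

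**The case against.** The strongest reply is that only a condensed article is shown, that covariate lists usually sit in an analysis plan, and that unadjusted comparisons are valid under randomization. Most of this stands for the adjustment. Chance imbalance is already allowed for in the type I error, and leaving out covariates biases nothing. It does not excuse the paired tests: the article names them, and they do not match its own aim or power statement.

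A reader might infer more than the documents support:

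- **That the plan contradicts its own Introduction.** The passage on baseline characteristics concerns which smokers succeed. The article follows it up by selecting motivated smokers and by an objective on predictors of success. It does not ask for adjustment for precision, and a Fagerstrom main effect would not answer its question.
- **That baseline is ignored altogether.** It enters through the change scores. What is absent is a covariate in a between-arm model.
- **That ignoring nicotine dependence costs a known amount of power.** The figures rest on an assumed joint r. At r = 0.1 to 0.2 the gain is at most 1.6 points, and nothing in the article links the Fagerstrom score to cough or other symptoms.
- **That adjustment is free everywhere.** With about 14 events it is not free for the primary outcome, and the stated sample size rests on the Z test.

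Finally, 40 blocks of 6 would give 80 per arm, or 64 at 80% retention. Unadjusted power for cigarettes/day is then already 89.7% (92.2% at r = 0.3), so the need for extra precision would be smaller.

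**Conclusion.** The point holds in two parts of unequal weight. First, the paired tests cannot deliver the comparison among arms that the same section promises and powers. This is a mismatch within the document and needs no assumption. Second, a between-arm model using baseline values already collected is a sensible improvement in efficiency. Its size is uncertain: at 49 per arm, from 80.4% power to between 80.8% (r = 0.1) and 90.2% (r = 0.5), less whatever a change score already captures. The sample size of 49 is correctly calculated, and the unadjusted Z tests for symptoms are valid and should remain the main analysis.

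**What to change.** In the Statistical Plan:

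1. Replace the paired t and signed rank tests with an ANCOVA of Month 6 cigarettes/day on treatment, baseline cigarettes/day and baseline Fagerstrom score. Report each between-arm difference with its confidence interval.
2. Keep an unadjusted two-sample comparison as a sensitivity analysis. It also preserves the link to the power statement. Within-arm changes can be reported descriptively.
3. For symptoms, keep the two-sided Z test as the main analysis. Add a baseline-adjusted standardized risk difference as supportive only. An adjusted odds ratio would not serve, because the gain in precision does not show as a smaller standard error on that scale.
4. Fix the covariates before unblinding. No stratification is needed.

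The cost is wording and modest analysis work, with no new data. The downside is the extra model assumptions of ANCOVA, which the unadjusted sensitivity analysis helps to check.

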### Design

This is a prospective, randomized, placebo-controlled, double-blind, three-parallel group study. The study protocol was designed using the recommendations of the Consolidated Standards of Reporting Trials statement (Figure 1).

For this study, we opted for the VP5 electronic cigarettes kit, which offered a good quality/price ratio and proven reliability and safety. Nicotine and nicotine-free liquids are produced by BioFumo, which fully collaborated with us and provided liquids in nicotine concentrations of 8 mg/mL and packages that were not distributed for commercial use.

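### Cigarette consumption is to be compared between three independent arms, but the tests named are paired tests, which only assess change within an arm

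*Protocol article*

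**What the plan says.** The Statistical Plan of the protocol article sets a between-group question for tobacco cigarettes: "A secondary analysis will assess the reduction of the consumption of tobacco-containing cigarettes after 6 months among the groups". The sentence that follows names the method: "Analysis will be based on paired Student’s t-test or the Wilcoxon signed rank tests". No other test is named for this analysis.

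The arms are independent. The Design section says: "This is a prospective, randomized, placebo-controlled, double-blind, three-parallel group study". Recruitment and Follow-Up describes the allocation as "40 blocks of 6 subjects randomly assigned to 1 of the 3 treatment groups". Nothing there matches a participant in one arm to a participant in another.

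Later in the Statistical Plan the same outcome gets a power statement built on a different test: "using a two-sided two-sample *t*-test with a significance level (alpha) of .05". The contrast for which that calculation is made is worded as "to detect a mean reduction of 5 cigarettes/day between any of the 2 experimental arms and the control arm". Its other inputs are 49 per arm, power 80%, a control-arm mean of 20/day and an SD of 8.7 in both arms.

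**The concern.** A paired t-test and a signed rank test both need matched pairs. Here the only pairs are a participant's baseline and Month-6 values. Applied to those, the tests ask whether consumption fell within one arm. They do not ask whether it fell more in one arm than in another, which is the question the plan sets and the one randomisation is there to answer.

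This matters particularly in this trial. Entry requires strong motivation to stop smoking (Participants), and every arm receives telephone cessation counselling (Treatments). Some fall in every arm, control included, is therefore likely with no e-cigarette effect at all. A set of within-arm p-values invites two misreadings: a significant fall in an e-cigarette arm is credited to the device, or a pattern of significant in one arm and not in the other is taken as a difference between them.

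The outcome is secondary, but it is not minor. Objectives calls the reduction of tobacco consumption a fundamental aim and frames symptom relief as its consequence, and the outcome has its own power calculation.

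**Working it through.** **Inputs from the Statistical Plan.** Difference 5 cigarettes/day; common SD 8.7; two-sided alpha 0.05; 49 per arm; retention targets of 80% at 6 months and 70% at 12 months. With 70 per arm (Sample Size), 70 × 0.80 = 56 at Month 6 and 70 × 0.70 = 49 at Month 12.

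**Assumed input.** The correlation r between baseline and Month-6 cigarettes/day is not given. I use 0.5, with a range of 0.3 to 0.7.

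**1. The plan's own figure.** For a two-sample t-test the noncentrality is (5/8.7) × √(49/2) = 0.575 × 4.950 = 2.84 on 96 degrees of freedom, which gives power 80.4%. Solving for 80% power gives 48.5, rounded up to 49. The stated figure is reproduced.

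**2. The same inputs under the test that is named.** The SD of a within-person change is 8.7 × √(2(1 − r)). The number needed for 80% power to detect a within-arm fall of 5/day is then:

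| r | SD of change | n for a paired t-test |
|---|---|---|
| 0.3 | 10.29 | 36 |
| 0.5 | 8.70 | 26 |
| 0.7 | 6.74 | 17 |

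None of these is 49. The stated power belongs to the two-sample test, not to the analysis described.

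**3. What separate paired tests show when the arms do not differ.** Give all arms the same true fall d. Let p be the power of the paired t-test within one arm of 56 (noncentral t, 55 degrees of freedom, noncentrality d√56 / SD of change). Two given arms disagree, one significant and one not, with probability 2p(1 − p). All three are significant with probability p³.

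| True fall in every arm | Disagreement, r = 0.3 | r = 0.5 | r = 0.7 |
|---|---|---|---|
| 1/day | 20% | 23% | 31% |
| 2/day | 42% | 48% | 48% |
| 3/day | 49% | 41% | 17% |

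Example at r = 0.5 and d = 2: p = 0.394, and 2 × 0.394 × 0.606 = 0.48.

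For a common fall of 5/day at r = 0.5, p = 0.988 and p³ = 96.5%, so all three arms are nearly always significant although no arm effect exists. The range is 85% (r = 0.3) to 99.9% (r = 0.7).

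**4. A between-arm test under the same null.** In simulation (20,000 trials, 49 per arm, r = 0.3 to 0.7, both arms falling equally by 2.5 or 5/day), the two-sample t-test on change rejected in 4.8% to 5.2% of trials. At the 2.5/day fall, separate paired tests disagreed in 41% to 50% of the same trials.

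**5. Power of the replacement.** ANCOVA on the Month-6 value has residual SD 8.7 × √(1 − r²):

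- r = 0.3: SD 8.30, power at 49 per arm 84%.
- r = 0.5: SD 7.53, power at 49 per arm 90%.

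The unadjusted two-sample comparison of Month-6 values has 80.4% at 49 per arm and 85.4% at 56. A two-sample t-test on change uses the SDs in step 2. At 49 per arm it has 66% power at r = 0.3 and 80.4% at r = 0.5.

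**The case against.** The strongest reply is that this is a slip in naming. The power statement shows that the authors intend a two-sample comparison of each experimental arm with control, so the section conflicts with itself rather than leaving out a between-arm comparison. That reading is plausible, and it explains why the sample size needs no change. It does not rescue the sentence: the only sentence that assigns a test to this analysis assigns the wrong one, and a power statement does not define the analysis.

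Second, the outcome is secondary and the primary symptom comparison, with its explicit arm contrasts and Z tests, is untouched. That is correct and limits the reach of the point.

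Third, if all arms fall by 5/day, the control arm is significant too, so a careful reader would see no difference; two given arms disagree in only about 2% of such trials at r = 0.5. This also stands. The misleading pattern of one significant and one non-significant arm arises mainly with moderate common falls.

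Fourth, the percentages depend on a correlation that the document does not give. They do, and the range is shown. They illustrate the risk and are not a measured error rate of this trial. That paired tests make no between-arm comparison holds at any correlation.

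Fifth, any unpaired test would cure the contradiction, and ANCOVA is a preference. That is fair as to the minimum repair. ANCOVA is still the better choice: a change-score t-test loses power if the correlation is below 0.5. Many Month-6 values may be zero because participants are asked to quit, which is a reason for a rank-based sensitivity analysis.

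**Conclusion.** The point holds. The plan poses a comparison among independent randomised arms and assigns it to tests that assess only within-arm change. It also contradicts the power statement in the same section, whose 49 per arm is reproduced by a two-sample t-test (80.4%) and not by a paired one (17 to 36). This is an error in what is written, not a detail left to another document.

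At 56 per arm and r = 0.5, arms with identical true falls of 1, 2 or 3/day give discordant paired tests in 23%, 48% and 41% of trials. These figures assume normally distributed values with SD 8.7 at both times; r is an assumption, with the range given in the working. The conclusion about the test depends on none of this. It should be corrected before the data are analysed; the article reports the trial as still recruiting.

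**What to change.** Replace the sentence that names the paired tests with wording such as: Month-6 cigarettes/day will be compared between arms by ANCOVA with treatment arm and baseline cigarettes/day as terms; each e-cigarette arm versus control, and nicotine versus nicotine-free, will be reported as a mean difference with a 95% confidence interval. The Wilcoxon rank-sum test on change from baseline will be the non-parametric sensitivity analysis. Changes within an arm will be reported descriptively, without tests.

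The nicotine versus nicotine-free contrast comes from the same model. It belongs in the list because the plan makes that comparison for the primary outcome and the Introduction expects a larger effect with nicotine.

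The cost is one sentence in the Statistical Plan. Baseline cigarettes/day is already needed for eligibility and for the secondary outcome itself. The sample size stays as it is, and the existing two-sample calculation is a conservative basis for the adjusted analysis.
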